#### Weekly goals

The long-term beverage goal for children was to consume no more than 4 fluid ounces of SSB/juice per day. An additional recommendation was to limit the 4 oz per day to 100 % fruit juice while eliminating all other sugar-sweetened beverages (i.e. fruit drinks, sweetened tea, flavored milk, regular soda, sports and energy drinks). The child’s goal for the first week was similar to their baseline level, but was gradually reduced to 4 oz per day (4 fl. oz. of SSB/juice = 1 serving for children) by week 8 of the program and remained there for the rest of the program (e.g. setting graded tasks). Mothers’ weekly beverage goal for the duration of the program was 8 oz or less (8 fl. oz. caloric beverages = 1 serving for mothers) of caloric beverages per day, which included all sweetened beverages described above plus milk (plain and sweetened), coffee with any caloric additions, and alcoholic drinks. An 8-oz. liquid measuring cup was provided to mothers so that they could measure exact 4-oz. (for children) or 8-oz. (for adults) beverage servings for the first week of the program in order to become accustomed to serving sizes. Mothers were also asked to limit the number of “red zone” foods they ate per day, which are high-calorie, high-fat foods from the Traffic Light Diet [33]. They were only asked to limit how many *times* per day they ate a red food, but were not asked to calculate calories or serving sizes. Their weekly red zone foods goal was set at half of their baseline intake. Mothers who were not consuming many caloric beverages at baseline, and thus did not have large beverage changes to make, were asked to put a greater emphasis on reducing their red zone foods. Because detailed measuring and self-monitoring of calories is time consuming, the simplified manner of measuring food and beverage intake in this study was intended to promote adherence to positive dietary changes and continued self-monitoring, as described below. Lastly, mothers had a goal to weigh themselves every day. Scales were not provided to participants, but participants who did not already have a scale were encouraged to purchase one.

#### Self-monitoring

Throughout the intervention mothers self-monitored their weight, their caloric beverage consumption, their intake of red zone foods, and their child’s SSB/juice consumption. Rather than tracking all calories, mothers checked a box in a simple, study-provided paper log each time they had a serving of a caloric beverage, each time they had a red zone food (regardless of caloric content), and each time their child had a serving of SSB/juice. At the end of each week, participants received a text message with a prompt to submit their weekly totals of caloric beverages servings, red zone foods, their last reported weight, and their child’s weekly total of SSB/juice.

#### Kick-off group session

Mothers randomized to the intervention condition attended a 75-min in-person kick-off session at the beginning of the study. They received information about the weight-related and dental consequences of consuming too many sugar-sweetened and non-nutritive beverages for both children and adults. Mothers were given their weekly goals and their child’s weekly goals and instructed on how to track their behaviors using the diaries and text messages. The session emphasized to mothers that making small, simple changes in their beverages and red zone foods would result in a reduction of 100–300 cal per day, which could lead to modest weight losses after several months. Mothers were encouraged to view their own weight loss efforts as a way to make healthy behavior changes in the home environment and be a positive role model for the benefit of their children’s health.

Participants were sent home with a “toolkit” of study materials, which included a printed copy of the first lesson, a chart with the mother’s and child’s personalized weekly beverage goals (gradual tailored progression), weekly self-monitoring diaries, sticker charts, stickers, and weekly prizes (described below), two 6-oz. cups with lids simple measuring of their child’s beverages, water bottles for the mothers and children, an 8-oz. liquid measuring cup, and a User’s Guide with program timelines and instructions on how to use the mobile website and text messaging components of the program.

#### Website and lessons

The Smart Moms website was created to provide short lessons and resources to help mothers change their own dietary behaviors and to work with their children to reduce their SSB/juice consumption. The website was responsive, or mobile-optimized, with content that was easily viewable on a smartphone so that mothers could access the information at any time. There were a total of 18 lessons that were updated weekly for the first 12 weeks and biweekly for weeks 13–24. They included information on behavioral strategies to reduce caloric beverages and red foods, but also incorporated topics on dietary intake, reading food labels, snacking, sleep, physical activity, screen time, communication and problem solving with their children, stress management, and relapse prevention strategies. Participants received a text message with a link to the study website indicating when the newest lesson had been posted.

#### Weekly tailored feedback

The weekly self-monitoring data submitted through text message were used to send participants tailored feedback. They received this personalized feedback through email, weekly for the first 12 weeks and biweekly for weeks 13–24. Generally, feedback messages were tailored to whether or not the child met their beverage goal for the week, whether or not the mother met her beverage goal for the week, whether she met her red foods goal for the week, and mothers’ weight loss progress.

#### Monthly progress check-ins

At the end of each month, participants received a link to a brief questionnaire that asked them to report which of the lessons they had read in the last month. Additionally, for goals they were not regularly meeting, they were asked to report the biggest barrier to change they experienced in the last month. This specific barrier was used to provide additional tailored feedback with strategies on overcoming the barrier in the next feedback email.

#### Tips, motivational messages, and goal progress assessment text messages

In addition to the lesson and self-monitoring prompts, all participants received an additional two text messages a week during the first half of the program and one additional text message per week during the second half of the program. These consisted of tips for behavior change, motivational messages, and goal progress assessments, which were brief multiple-choice questions about the progress that mothers were making towards one of the behaviors that week. Based on their answer, a tailored feedback message was sent in response that usually consisted of encouraging them to continue their good progress or providing them with support if they were having difficulty. These messages were sent at random intervals, as that has been shown to increase the effectiveness of SMS-based interventions [34].

#### Child reinforcement charts

Mother/child dyads were given 12 colorful, engaging weekly charts to track the child’s beverages together with their child as well as stickers and 12 token prizes (e.g. $1 toys, games, etc.). Each chart stated the child’s beverage goal for that week, and the mothers were instructed to have their child put a sticker on each day that they met their beverage goal. If the child met their weekly beverage goal, the mother gave them a prize at the end of the week. Although there was no specific goal for water consumption, the study also provided mother-child dyads with additional sticker charts to encourage the child to drink more water. Children placed a sticker on the chart each time they had a glass of water and mothers were encouraged to give them a prize when the chart was full. The charts and prizes served to increase positive reinforcement for the child’s SSB/juice and water changes during the first half of the program. The study did not provide these charts and prizes after week 12, but mothers were encouraged to use the same principles and to continue with charts and prizes of their own throughout the remainder of the program.

### Control group procedures

The modified waitlist control group attended one group session where they received their randomization assignment and were encouraged to continue with their normal behaviors for the next 6 months. Because of the nature of a control group, contact was limited with control group participants. However, they completed assessment visits at the same time as treatment group participants and received incentives (described below) for doing so. The face-to-face contact they received with the principal investigator at the 3-month assessment may have encouraged retention at 6 months. They received a modified version of the intervention following the 6-month assessments.

### Measures

Participants completed assessments at baseline (prior to randomization), 3 months, and 6 months. Each assessment period included an in-person visit and the completion of online questionnaires. Participants in either treatment group who missed assessment visits were contacted frequently by phone and email to schedule and complete assessment visits. Participants received a $20 honorarium for completing each of the 3- and 6-month assessments, meaning participants who completed both assessments received $40 total.

#### Demographics

A lifestyle questionnaire assessed demographics at baseline, including age of the mother and child, race/ethnicity, income, maternal employment status, maternal education, marital status, number of children in the home, and whether the child was in childcare or kindergarten (hereafter referred to as childcare status).

#### Anthropometrics

Trained research staff measured the height and weight of both mothers and children in light clothing (without shoes). Due to limited staffing, the principal investigator, who was not blinded to treatment condition, conducted the anthropometric measurements. Weight was measured using a digital Tanita scale to the nearest 0.1 kg. Height was measured using a wall-mounted stadiometer to the nearest 0.1 cm. The weight and height of mothers was converted to BMI (kg/m^2^) and weight was used to calculate percent weight loss. The height, weight, age, and gender of children was used to calculate BMI z-score using the Centers for Disease Control and Prevention growth curves [35].

#### Sugar-sweetened beverage intake/Diet

Mothers completed a single 24-h dietary recall for her own intake and another 24-h recall in which she reported her child’s intake at each assessment period. Trained research assistants that were blind to treatment group assignment completed the dietary recalls in order to avoid any biases. Because the goal of the Smart Moms study was to impact maternal practices of providing children with SSBs or juice within the home environment, the mother-reported child recall included only food and beverages that the parents provided the child. Any food or beverages purchased at or provided by childcare, school, or another care provider were not included in the dietary recall. The dietary data were entered into the Nutrition Data System for Research (NDSR), which was used to generate reports of the child’s SSB/juice intake in fluid ounces per day, mothers’ caloric beverage intake in ounces and calories per day, in addition to other dietary variables such as total calories, fat, and added sugars.

#### Physical activity

To assess maternal physical activity, mothers completed the Paffenbarger Physical Activity Questionnaire [36]. It has been used to assess leisure time activity in many weight loss trials and can be scored to provide an estimate of minutes per week and calories expended per week in overall leisure time activity. This questionnaire was administered during the in-person assessment visit by trained study staff. Child physical activity was assessed with the physical activity module of the Children’s Physical Activity Questionnaire [37]. This questionnaire was completed online and asked the mother to report, in the last 7 days, how many times and for how long the child did each of 28 activities. It has been validated against accelerometry in children ages 4–5, with a correlation of 0.42 between self-report measurement of MVPA and measurement of MVPA from accelerometers.

#### Social cognitive mediators

There are no existing validated questionnaires that measure theoretical constructs specific to parents reducing the SSB consumption of young children. Therefore, this study used a series of questions drawn from several previous research studies and developed specifically for use in this study. To assess self-efficacy for reducing their child’s SSB consumption and other behaviors, mothers completed six items from a previous study that assessed their confidence in making obesity-related changes with their children [38]. In the cited study, the items had high internal consistency (α = 0.72). An additional three items adapted from a previous study [39] were added to assess self-efficacy for making changes in the child’s SSBs and outcome expectations for limiting SSBs. Mothers’ frequency of setting limits with SSB consumption and other behaviors was assessed with nine items used and adapted from a previous study [40]. The questions assessed mothers’ agreement with restricting SSB/juice consumption, TV time, and fast food consumption.

#### Home environment

Mothers completed several online questionnaires that assessed the social and physical aspects of the food and physical activity home environments. The physical food environment was assessed using a measure developed for a previous family-based study [41], in which mothers reported whether or not each of 71 food items was present in the home in the last week. The social food environment was assessed with the Meals in Our Household questionnaire [42]. The questionnaire consisted of 50 items across 6 subscales: structure of family meals, problematic child mealtime behaviors, use of food as a reward, parental concern about child’s diet, spousal stress related to child’s mealtime behaviors, and influence of child’s food preferences on what other family members eat.

#### Maternal sedentary behavior

In addition, mothers’ self-report of sedentary behavior was measured with the Sedentary Behavior Questionnaire [43], which asks participants to report the number of hours they spend in a wide range of sedentary activities (watching TV, playing computer or video games, sitting down while listening to music, on the telephone, or doing work or crafts, and sitting down during transportation) on an average weekday and weekend day. In the validation sample, test-retest reliability coefficients ranged from 0.51 to 0.90.

#### Child screen time

Child screen time was measured with six screen time questions adapted from a well-known screen time intervention [44]. Mothers reported the child’s average total screen time over the prior 7 days (during the time that the child was home) for (1) TV/DVDs, (2) playing video games, (3) using the computer, and (4) viewing or playing games on a smartphone or tablet. Mothers estimated for each category the average hours per weekend day and average hours per weekday. The categories are summed together, and from that, an average amount of screen time per day will be calculated (Average screen time = [[weekday time × 5] + [weekend time × 2]]/7).

#### Parent feeding styles

The Parental Feeding Style Questionnaire [45] is a 27-item questionnaire that is used to assess four aspects of feeding style: emotional feeding, instrumental feeding, prompting/encouragement to eat, and control over eating.

#### Depression

Mothers’ depressive symptoms were assessed with the Center for Epidemiologic Studies Depression Scale Short Form, a 10-item self-report measure that measures depressive feelings and behaviors during the past 7 days [46].

### Data analysis

SAS version 9.3 (Cary, NC) will be used to conduct statistical analyses for the primary and secondary analyses of this intervention. Intent-to-treat analyses using linear mixed models will be used to examine changes in the primary and secondary outcomes. The linear mixed models will include a random intercept and effects for treatment group, time, and group by time interactions for both follow-up visits. A Bonferroni adjustment will be used to account for the effect of comparisons at multiple time points. Any characteristics found to be associated with both treatment group and the outcomes will be defined as confounders and will be included as covariates in analyses.

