### Sample size and statistical analysis

The primary outcome for the study was change in child SSB/juice intake in fluid ounces from baseline to 6 months. Based on evidence from three previous studies that resulted in significant SSB/juice reductions in children [14, 29, 30], the study was powered to detect a difference of a 6-oz reduction between groups at 6 months, with a within-group standard deviation of 6.0. Therefore, with 80 % power at an alpha level of .05 and accounting for 20 % attrition, the study required 21 participants per group for a minimum of 42 total participants to detect a significant difference in SSB/juice reduction.

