## Discussion

This study was designed to determine whether a low-burden intervention delivered using mobile methods and targeted towards mothers could be effective at changing child sugar-sweetened beverage intake. There is a critical gap in the literature such that few interventions have been successful at modifying parent and child weight-related behaviors. This is the first randomized controlled trial intended to determine the efficacy of an innovative mobile-based program to change behavior in mother-child dyads.

Though the study is innovative in its design and goals, there are several limitations. First, in order to limit measurement burden on mothers, the outcome of SSB/juice intake was measured by a 1-day 24-h dietary recall, versus the gold standard of 3days of dietary recall data. This is a limitation, as SSB/juice intake likely varies considerably from day to day. However, because the dietary recall data was being used to compare average dietary values between groups, intra-individual variability is less of an issue. Thus, the use of only one dietary recall in this study was the best choice for dietary and SSB/juice assessment in this population. Additionally, the self-reported nature of the SSB/juice and dietary data could be a potential limitation of the study, although use of the 24-h recall is the current standard in behavioral interventions, and research assistants were blinded to treatment group in order to mitigate the risk of bias.

Lastly, this intervention targeted solely an overweight or obese mother as the agent of change due to the well-known strength of association between child and maternal weight and dietary behaviors. However, the intervention did not directly target or involve any other family members living in the home, including fathers, partners, and other children. If the father is overweight or obese [47], and if there are additional children in the home who potentially increase parental barriers to making dietary and physical activity changes, then it may not be sufficient to target only the mother while overlooking the other family members.

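### The mixed model leaves the arms' baseline means free, so the primary test rests on raw change from one recall: valid, but less precise than a baseline-adjusted analysis

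*Protocol article*

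**What the plan says.** All references are to the protocol article.

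- **Endpoint** (Sample size and statistical analysis): "The primary outcome for the study was change in child SSB/juice intake in fluid ounces from baseline to 6 months".
- **Model** (Data analysis): "The linear mixed models will include a random intercept and effects for treatment group, time, and group by time interactions for both follow-up visits". With only two follow-up visits, a group effect plus an interaction at each of them makes sense only if baseline is a third response visit.
- **Covariates** (Data analysis): a characteristic enters the model only if it turns out to be related both to arm and to outcome. Neither baseline intake nor the stratification factors are named as model terms.
- **Multiplicity** (Data analysis): a Bonferroni adjustment is applied across time points.
- **Measurement** (Sugar-sweetened beverage intake/Diet): one 24-hour recall of the child's intake per assessment. The Discussion concedes that "SSB/juice intake likely varies considerably from day to day".
- **Randomisation** (Study design): carried out after baseline data collection, and stratified by childcare status and by the child's baseline intake. The number of intake levels is not given.
- **Planning figures** (Sample size and statistical analysis): "the study was powered to detect a difference of a 6-oz reduction between groups at 6 months". The SD within each group is put at 6.0 oz, without saying whether it is the SD of change or of intake at one visit. Power is 80%, alpha .05 and attrition 20%, which leads to 21 dyads per arm, or 42 in all.

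**The concern.** Because baseline was measured before allocation, any difference between the arms there is chance. The treatment main effect estimates a quantity known to be zero, and its sampling error passes into the 6-month contrast. A change score subtracts the whole of the baseline value, whereas the best predictor of follow-up uses only the fraction ρ of it. The lower ρ is, the more noise the change score imports. A single recall of a behaviour that varies from day to day points towards a low ρ.

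The Discussion argues that within-person variation matters less when group averages are compared. That is right for bias but not for variance: the variation enters the contrast at both visits.

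The covariate rule does not repair this. It brings baseline intake in only if intake happens to be associated with both arm and outcome, so the gain is left to chance. In a trial with a minimum of 42 dyads, what is at stake is the width of the confidence interval and the power of the primary test.

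**Working it through.** **1. The plan's own figure.** Inputs: difference 6 oz, SD 6.0, 80% power, alpha .05 (taken as two-sided), 20% attrition.

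- Normal approximation: 16 per group; 16/0.8 = 20.
- t test: 17 per group (power 80.7%); 17/0.8 = 21.25, rounded up to 22; or 17 × 1.2 = 20.4, rounded up to 21.

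The stated 21 per group reproduces within rounding. I use 17 completers per arm below.

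**2. Variance of the two contrasts.** Let s be the SD at each visit (assumed equal) and ρ the baseline-to-follow-up correlation (assumed; the article gives none). Per-arm variance with complete data:

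- free baseline means (raw change): 2s²(1 − ρ)
- common baseline mean, or baseline as covariate: s²(1 − ρ²)
- ratio: (1 + ρ)/2, so the saving is (1 − ρ)/2

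| ρ | saving |
|---|---|
| 0.2 | 40% |
| 0.4 | 30% |
| 0.7 | 15% |

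**3. Allowing for dropout and stratification.** The three-visit random-intercept model was simulated with 21 per arm, 20% random dropout after baseline, s = 6 and randomisation stratified by a median split on baseline intake (the split is an assumption). Strata were left out of the fitted model, as in the plan. Entries are variances of the 6-month contrast, free baseline → common baseline.

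| ρ | variance the model reports | true sampling variance |
|---|---|---|
| 0.2 | 6.36 → 4.16 (−34.5%) | 5.01 → 4.04 (−19%) |
| 0.4 | 4.89 → 3.66 (−25%) | 4.37 → 3.85 (−12%) |
| 0.7 | 2.53 → 2.22 (−12%) | 2.29 → 2.13 (−7%) |

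Under the planned model the reported variance exceeds the true one (6.36 against 5.01 at ρ = 0.2). Stratification has already removed part of the baseline imbalance, but the model does not know it, so its standard error is too large.

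**4. Power at the level the plan will use.** Bonferroni over two follow-ups (assumed) gives .05/2 = .025. Noncentral t with 17 per arm, 32 degrees of freedom and noncentrality 6/(SD × √(2/17)), before allowing for stratification:

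*If 6.0 is the SD of change.* The effective adjusted SD is 6√((1 + ρ)/2).

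| ρ | adjusted SD | power, raw change | power, adjusted |
|---|---|---|---|
| 0.2 | 4.65 | 71.2% | 91.5% |
| 0.4 | 5.02 | 71.2% | 86.5% |
| 0.7 | 5.53 | 71.2% | 78.7% |

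*If 6.0 is the SD of intake at one visit.* The change SD is 6√(2(1 − ρ)) and the adjusted SD is 6√(1 − ρ²).

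| ρ | change SD | power | adjusted SD | power |
|---|---|---|---|---|
| 0.2 | 7.59 | 48.9% | 5.88 | 73.1% |
| 0.4 | 6.57 | 62.4% | 5.50 | 79.2% |
| 0.7 | 4.65 | 91.5% | 4.28 | 95.3% |

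**5. Unequal variances.** With k = baseline SD / follow-up SD, the ratio for the covariate analysis is (1 − ρ²)/(1 + k² − 2ρk). At k = 0.7 the saving is 21%, 10% and 0% for ρ = 0.2, 0.4 and 0.7. At k = 1.3 it is 56%, 49% and 41%.

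**The case against.** The strongest reply is that nothing here is misstated. The endpoint is change, the model estimates the difference in change without bias under randomisation, and it is a standard choice. That stands: this is an efficiency point about a valid analysis.

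Second, stratifying on baseline intake already limits chance imbalance. This also stands, and it shrinks the real gain (step 3). A reader might infer that the baseline noise is carried into the estimate in full; the Study design section rules that out. What remains is the smaller true saving, plus an overstated standard error because the strata are not in the model.

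Third, a reader might take a saving of 15–40% as a property of this trial. The article does not support that. The range is simply ρ = 0.7 to 0.2 with equal variances and complete data. Equal variances are open to doubt: entry required at least 12 oz a day and the programme aimed for no more than 4 oz. Step 5 shows that the saving could be smaller or larger.

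Fourth, a full analysis plan may settle how baseline is parameterised. It may, but the article does more than stay silent: it names a treatment-group effect and an imbalance-driven covariate rule. The wording as published should be changed.

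**Conclusion.** The point holds as a recommended improvement. The model as written tests raw change from a single-recall baseline and uses baseline intake as a covariate only if chance makes it look like a confounder. Sharing the baseline mean or adjusting for baseline reduces the variance by (1 − ρ)/2 under equal variances and complete data. With the planned dropout, the reduction is about 12–35% in the variance that drives the test and interval. It is about 7–19% in true sampling variance if stratification was a median split. If 6.0 oz is the SD of change, power at .025 goes from about 71% to about 79–92% for ρ = 0.7 to 0.2, before allowing for stratification. All of these rest on an assumed ρ.

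A reader might also conclude that the primary result will be biased or its test invalid. It will not: leaving the strata out makes the test conservative.

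**What to change.** Before analysis, replace the model sentence with one of the following:

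- drop the treatment main effect, so that both arms share one baseline mean, and keep the group-by-time terms at 3 and 6 months; or
- model the 3- and 6-month values as responses, with baseline intake (and baseline-by-visit) as a prespecified covariate.

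In either case include the stratification factors, childcare status and baseline-intake stratum, and report the 6-month arm difference as the primary estimate. State whether the SD of 6.0 refers to change or to intake at one visit. An unstructured covariance is optional: it has six parameters for three visits against two for the random intercept, and this gain does not need it.

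Cost: a change of wording and no new data. The covariate takes about one degree of freedom (one more if baseline-by-visit is included), and the strata take their own. Dropping the main effect frees one parameter.

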## Methods/Design

### Study design

Smart Moms is a two-group randomized controlled trial designed to test the efficacy of a 6-month program to reduce SSB and juice consumption among children ages 3–5 of mothers who are overweight or obese compared to a waitlist control group. Mother-child dyads were randomly assigned to the Smart Moms intervention group or to a waitlist control group after baseline data were collected. Randomization was stratified by two factors: whether or not the child was in childcare/kindergarten and child baseline SSB/juice intake. The primary hypothesis is that the Smart Moms program will result in a greater reduction in child fluid ounces of SSBs and juice compared to the control group at 6 months. Secondary outcomes include maternal percent weight loss, maternal caloric beverage consumption, and child BMI z-score at 6 months. The study was approved by the UNC non-biomedical IRB on March 18, 2014.

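### A random intercept as the only named covariance feature is likely to understate the 6-month standard error for maternal weight change, and the Bonferroni step does not repair this

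*Protocol article*

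**What the plan says.** The protocol article, Data analysis, sets one approach for all main outcomes: "Intent-to-treat analyses using linear mixed models will be used to examine changes in the primary and secondary outcomes". The model is then described: "The linear mixed models will include a random intercept", along with group, time and their interaction at each of the two follow-up visits. The next sentence adds: "A Bonferroni adjustment will be used to account for the effect of comparisons at multiple time points". No residual covariance, visit-specific variance or robust standard error is named.

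Under Study design, maternal weight is among the secondary outcomes: "Secondary outcomes include maternal percent weight loss, maternal caloric beverage consumption, and child BMI z-score at 6 months". Under Anthropometrics, "weight was used to calculate percent weight loss". Under Measures, "Participants completed assessments at baseline (prior to randomization), 3 months, and 6 months".

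Interaction terms for the two follow-up visits suggest that baseline is the reference visit. The article does not say so outright. It also does not say whether percent weight loss enters the model with a baseline row of 0, or whether weight itself is modelled. It gives no SD or correlation for maternal weight.

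**The concern.** With nothing added, a random intercept implies compound symmetry: the same variance at baseline, 3 and 6 months, and the same correlation for each pair of visits. The model estimates one residual variance and uses it for every contrast.

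Weight change does not usually behave that way. Mothers start from a common zero and drift apart, so change from baseline to 6 months tends to vary more than change from baseline to 3 months or from 3 to 6 months. A pooled residual variance averages the three. The 6-month contrast then gets a standard error that is too small, an interval that is too narrow and a test that rejects too often. In a trial planned for about 42 dyads, a weight-loss claim could rest on that.

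**Working it through.** **Inputs from the article.** Sample size section: 21 per group, 20% attrition, 80% power, and a test "at an alpha level of .05" (two-sided assumed). Data analysis: Bonferroni over two follow-up visits, so 0.05/2 = 0.025 per visit.

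**The plan's own figure.** The article states no error rate for the weight test. Its sample size reproduces: a 6 oz difference with SD 6.0 needs 17 per group by the exact t-test (power 80.7%), and 17 × 1.2 = 20.4, which rounds up to 21. I use 17 per arm as the number analysed.

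**Assumptions, not in the article.** SD of change 2.5–3 at 3 months and 3.5–5 at 6 months, correlation 0.8 between the two. Wider range: ratio r of the 3-month to the 6-month SD from 0.5 to 1.0, correlation ρ from 0.6 to 0.9.

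**Formula.** With complete data on three visits, each mother's within-subject sum of squares is one third of the sum of her three squared pairwise differences, on 2 degrees of freedom. So the residual variance estimates one sixth of the summed pairwise difference variances. The model variance of 6 months minus baseline, twice the residual variance, is therefore their mean:

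model variance = [V(0,3) + V(0,6) + V(3,6)]/3; true variance = V(0,6).

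For SDs 2.5 and 4: V(0,3) = 6.25, V(0,6) = 16, V(3,6) = 6.25 + 16 − 2(0.8)(2.5)(4) = 6.25. Mean = 28.5/3 = 9.5 against 16. SE ratio = √(9.5/16) = 0.771.

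Approximate type I error is 2[1 − Φ(ratio × z)], with z = 2.241 at 0.025 and 1.960 at 0.05:

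| SD at 3 / 6 months | Model / true variance | SE ratio | 6-month error at 2.5% | 6-month error at 5% |
|---|---|---|---|---|
| 2.5 / 4 | 9.50 / 16 | 0.771 | 8.4% | 13.1% |
| 3 / 4 | 10.27 / 16 | 0.801 | 7.3% | 11.6% |
| 2.5 / 5 | 14.17 / 25 | 0.753 | 9.2% | 14.0% |
| 3 / 3.5 | 8.57 / 12.25 | 0.836 | 6.1% | 10.1% |

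**Simulation** (20,000 null trials per scenario, 17 per arm, complete data): 6.4–9.0% for the 6-month test at 0.025, and 7.4–9.0% for a false positive at either visit against 5%. At an unadjusted 0.05 the four scenarios gave 13.1%, 11.6%, 13.6% and 10.2%. A plain t-test of change at each visit gave 4.7–5.3%.

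**Where the excess sits.** With ρ = 0.8, r = 0.6 to 0.8 and 21 per arm, the 3-month test at 0.025 rejected 0.6–2.3% of the time. The problem is at 6 months.

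**Wider assumptions.** The SE ratio runs from 0.73 to 0.97, the 6-month error at 0.025 from about 3% to 10%, and familywise error from about 5% to 10%. With equal follow-up SDs and ρ = 0.5 the mean is (1 + 1 + 1)/3 = 1 and there is no inflation.

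**Weight in kg.** The formula uses only differences between visits, so the spread of baseline weight cancels. Simulation with a baseline SD of 15 gave 8.2%, 7.4%, 9.1% and 5.8% at 0.025 for the four scenarios.

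**Follow-up values only, still with a random intercept.** About 2.5–7% at 0.025, with no inflation when the two SDs are equal.

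**The case against.** **The sentence does not exclude more structure.** To include a random intercept is not to rule out a residual covariance or robust standard errors, and a journal article may leave these to an analysis plan that is not shown. If that plan specifies them, the point falls away. But the article does name a covariance feature, only one, and applies it to every main outcome. Taken as written, that is a choice and can be judged as one.

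**The inputs are assumed.** This stands. Nearby assumptions shrink the effect: with SDs 3.5/3.5 and ρ = 0.8 the 6-month error at 0.025 is 4.4%; with 3.5/4 and ρ = 0.6 it is 4.0%; with 4/4 and ρ = 0.6 it is 2.9%. The size is uncertain. The direction held throughout the range examined.

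**The zero baseline row is inferred.** Also true, but the result does not need it, as the kg calculation shows.

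**Stronger readings.** A reader might infer that the maternal weight test runs at 10–14% instead of 5%. That is the unadjusted test, whereas the article applies a Bonferroni adjustment in the next sentence.

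A reader might also infer that the primary test on child intake is inflated. The article does not support this. Entry at 12 oz or more a day truncates the baseline distribution and could make its SD smaller than at follow-up, while the goal of 4 oz a day could shrink the follow-up SD. At ρ = 0.3 and nominal 5%, error is 3.7–4.6% with a smaller baseline SD and 6.3–7.1% with a larger one.

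**Conclusion.** The point holds for maternal weight change. A random intercept alone does not fit an outcome whose variance of change grows over time, and the 6-month standard error is then too small. Under the four assumed scenarios the 6-month test has about 6–9% type I error against 2.5%, and about 7–9% familywise against 5%. Over the wider range the 6-month figure is about 3–10%. Bonferroni lowers the rate but leaves the standard error wrong.

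This rests on the random intercept being the whole covariance specification, on interactions measured from baseline, and on SDs and correlations that the article does not give. The affected outcome is secondary. No inflation is claimed for the primary outcome, and the sample size is untouched. The change is worth making because it is nearly free.

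**What to change.** Replace the random intercept with an unstructured covariance over the visits, fitted by REML with a small-sample degrees-of-freedom correction such as Kenward-Roger. For child intake this gives valid standard errors whichever way the variances differ. The Bonferroni step can stay.

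Maternal percent weight loss needs its own sentence, because a constant-zero baseline row cannot enter an unstructured model. Either model only the 3- and 6-month values with baseline weight as covariate, or model log weight at all three visits.

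The cost is one line of SAS code and a sentence of text. Covariance parameters rise from two to six with three visits, or to three with two visits, which 42 dyads can support. The 6-month interval for maternal weight will be wider. In the four scenarios the corrected standard error is 1/0.836 = 1.20 to 1/0.753 = 1.33 times the random-intercept one, which is uncertainty the stated model would hide.
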